**Figure 2 F2:**
[figure not shown]
PROLUCA Study Timeline (three intervention groups and one control group).

### Blinding

It is not possible to blind the participants to their actual treatment allocation, since participants are aware whether they initiate preoperative exercise and whether their postoperative exercise starts two or six weeks after surgery. All study personnel collecting data and doing the statistical analyses of the data are, however, blinded to the patient allocation, and the patients are strictly informed not to reveal their group allocation to the test personnel.

### Exercise training protocols (General considerations)

#### ***Preoperative exercise***

The home-based exercise program is individually designed for each of the participants randomized to a preoperative intervention. The ultimate goal of the preoperative home-based exercise program is to ensure that the patients perform cardiovascular exercise of moderate-vigorous intensity (~60-80% of maximum heart rate (HRmax)) for at least 30 minutes every day until surgery. The preoperative period varies in length and the intention is not to exceed 14 days. The preoperative exercise is monitored by a heart rate sensor (Polar Team 2 System, with off-line transmitters) and an exercise diary logbook.

#### ***Postoperative rehabilitation***

The postoperative intervention consists of a supervised 12-week rehabilitation program containing 24 group-based exercise sessions, three individual counseling sessions, and three group-based lessons in health-promoting behavior. If the participants have special needs in terms of smoking cessation, nutritional counseling or patient education, this is offered too.

The postoperative physical exercise consists of an individually prepared supervised strength exercise – and a group-based cardiovascular exercise twice a week (60 minutes/session) on non-consecutive days for 12 weeks, a total of 24 sessions, containing the following elements:

Warm-up (five minutes) and cardiovascular exercise (25 minutes) on ergometer bike (BODY BIKE Classic Supreme©), individually prepared strength exercise (25 minutes) carried out using five machines (Technogym™), leg press, chest press, leg extension, pull to chest, pull-down (upper body). The practical aim of strength exercise is to complete three series of 5–12 sets. Trained physiotherapists and cancer nurse specialists supervise the training program following the recommended principles [50]. All exercise sessions will include supervised breathing exercises combined with stretching and relaxation techniques (five minutes). All the cardiorespiratory exercise is designed such that participants begin exercising at a low intensity (~50%-60% of individually determined HRmax) which is subsequently increased to more moderate to vigorous intensity (~70%-80% of individually determined HRmax). The ultimate goal for the postoperative exercise is two group-based exercise sessions per week, with a cardiorespiratory intensity for the first four weeks at ~50-60% of individual HRmax. The next eight weeks the intensity increases to moderate-high intensity at ~70-90% of individually determined HRmax. The heart rate will be monitored continuously throughout the cardiorespiratory exercise using heart rate monitors and software (Polar Team^2^ Pro©). All interventions will be individually tailored to each participant and following the principles of aerobic or resistance training prescription guidelines for adults as recommended by the American College of Sports Medicine (ACSM) [50]. The ultimate goal for the strength exercise program is to exercise with an intensity of ~60-80% of 1 RM two times a week for 12 weeks. To ensure progression every second week, the load is progressively increased and the number of repetitions are reduced starting out at 12 repetitions in three sets progressing to 10 repetitions in three sets to a final of eight repetitions in three sets. The progression is documented in a study exercise log file for registration of the intensity of all sessions along with data on blood pressure prior to exercise.

#### ***Adherence Considerations***

To maximize adherence, several strategies will be employed including telephone-based follow-ups. The patients are provided free parking in front of the center and transport expenses are covered. The high degree of scheduling flexibility allows participants to perform test at a convenient time and work around other competing demands such as medical appointments, work, and family commitments.

### Study endpoints and assessments

#### ***Primary endpoint***

VO_2_peak is evaluated by an incremental test using an electromagnetically braked cycle ergometer (Lode Corival Ergometer©). Inspired and expired gases are analyzed breath-by-breath by a metabolic cart (JAEGER MasterScreen CPX©). Subjects begin pedaling at seven watts and resistance increases after a predefined 10 watts ramp protocol until exhaustion or a symptom-limited VO_2_peak is achieved (pain, dizziness, anxiety etc.). This regimen has previously been demonstrated to be appropriate for measuring VO_2_peak in prior studies in patients with ankylosing spondylitis [51]. Other similar VO_2peak_ protocols are found appropriate for measuring VO_2_peak in NSCLC [38,39,52].

#### ***Secondary endpoints***

##### 

**Patient-reported outcomes (PROs)** PROs will include HRQoL, symptoms and side effects, anxiety and depression, well-being, distress, lifestyle, sickness absence, work status, and social support. HRQoL is assessed using the integrated system of the European Organization for Research and Treatment in Cancer (EORTC) for assessing the HRQoL of cancer patients participating in international clinical trials and devised through collaborative research. The EORTC QLQ-C30 assesses patient symptoms and HRQoL in lung cancer patients [53]. Symptoms and side effects will be assessed using the EORTC–LC13, which is an additional page to the EORTC-QLQ specifically designed to cover a wide range of lung cancer patients varying in disease stage and treatment modality [54]. EORTC measures single items and the scales range in score from 0 to 100. A high scale score represents a higher response level. A high score for a functional scale represents a high/healthy level of functioning and a high score for the global health status/quality of life represents a high HRQoL. However, a high score for a symptom scale/item represents a high level of symptomatology or problems [53,54].

HRQoL will also be assessed using the Functional Assessment of Cancer Therapy - Lung (FACT-L) scale that contains four subscales for physical (7-items), functional (7-items), emotional (6-items), social/family well-being (7-items) plus a lung cancer specific subscale (15-items) which will be summed to obtain the FACT-L score (all 42 items) [55].

General well-being is assessed using the 36-Item Short Form Health Survey (SF-36), standard recall (four weeks). The SF-36 includes eight scales measuring general health with two summary scales; physical and mental component scales [56,57]. To assess psychological well-being, the Hospital Anxiety and Depression Scale (HADS) with 14 items will be administered, designed to measure general anxiety and depression for use in investigations of patients with physical illness [58]. The distress thermometer is a validated measure of distress and consists of a single item, with responses ranging from 0 to 10 [59].

The Multidimensional Scale of Perceived Social support (MSPSS) is a 12-item scale assessing social support. Each item is answered on a seven-point Likert scale, from one: Very strongly disagree, to seven: Very strongly agree. The scale yields three subscale scores, for Family, Friends, and Significant Others, and a Total score, which is confirmed in a confirmatory factor analysis [60]. In other different cancer studies, all the above-mentioned validated instruments were found appropriate and easy to administer [35,52,59,61].

#### ***Physiological measurements***

Physiological measurements will include: (1) functional capacity, (2) pulmonary function, (3) cardiovascular O_2_ delivery, and (4) muscle strength. (1) functional capacity will be measured by a six-minute walking distance (6MWD) test carried out over a pre-measured distance of 22 m and in accordance with the American Thoracic Society (ATS) statement [62]. The 6MWD test has demonstrated good reliability and validity in patients with chronic obstructive lung disease [63], a patient group with similar symptomatology and pathophysiology. (2) Pulmonary Function will be determined by assessing the Forced Expiratory Volume in one second (FEV_1_), and the FEV_1_% which is the ratio of FEV_1_ to the Forced Vital Capacity (FVC) using a Triple V digital volume sensor© connected to JAEGER MasterScreen CPX©. All pulmonary function tests will be performed in a standing position and according to the ATS guidelines [48]. (3) Arterial O_2_ Saturation will be assessed at rest and continuously during exercise using pulse oximetry (Nellcor, OxiMax N-65©), which provides the most accurate non-invasive assessment of blood arterial O_2_ saturation levels. Muscle strength is measured by 1RM [64] using machines (Technogym™) that includes leg press (lower extremity) and chest press (pectoral muscles).

#### ***Disease-related outcomes***

In all patients lung cancer subtype, stage and extent of surgery will be related to the effect of exercise and rehabilitation interventions.

#### ***Tracking and monitoring of adverse events***

Tracking and monitoring of adverse events are assessed as follows: (1) before every intervention- and test-session, all patients will receive face-to-face supervision by a specialized trained cancer nurse discussing any potential negative side effects of the intervention assignment. All injuries and adverse events (e.g., knee pain, back pain) will be recorded as unintended events. In addition, heart rate and blood pressure are recorded prior to every intervention session and repeated if any adverse events should occur during exercise.

### Statistical considerations

#### ***Sample size calculation***

This randomized phase II trial will accrue 380 subjects with operable NSCLC over an accrual period of ~2 years. The present design consists of four intervention groups of equal size, and it is assumed that no interaction occurs between the groups. With the smallest clinical relevant difference set at 2 mLO_2_^.^ kg^-1 .^ min^-1^,95 participants are required in each group (power: 80%), giving a total inclusion of 380 patients.

For each of the primary and secondary endpoints, three separate t-tests will be used to compare each experimental arm to the control arm in mean change across time of the endpoint. For each endpoint, the overall alpha level will be controlled at a two-sided 0.05 by using Holm's procedure [65]. That is, Holm's procedure first ranks the three p-values from lowest to highest. The first (lowest) p-value has to be less than 0.05/3 (0.0167) to be significant and permit continuation to the other t-tests. The Holm's procedure continues sequentially in this fashion using alpha levels of 0.05/2 (0.025) and 0.05/1 (0.05) for the remaining two t-tests, respectively. Power for this study is defined as the probability that at least one of the three t-tests of the arm effect on VO_2_peak is significant; in other words, power is the probability that the first of the 3 ordered t-tests are significant. We assume that change in VO_2_peak will have a standard deviation of 4.0 mL ^.^ kg^-1 .^ min^-1^ as observed in previous research [27,36]. Statistical power depends upon the configuration of mean change in VO_2_peak across the 4 arms. Thus, for example, 80% power is obtained when the mean change in VO_2_peak across Arms 1, 2, 3, and 4 is 0.60, 0.60, 2.10, and 0.0 (mL ^.^ kg^-1 .^ min^-1^), respectively.

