### Procedure

The study is conducted in accordance with the CONSORT (Consolidated Standards of Reporting Trials) statement for non-pharmacologic interventions and the Helsinki Declaration [49]. Informed consent is obtained from all participants prior to initiation of any study procedures. The study is approved by The Danish National Committee on Health Research Ethics (H-3-2012-028) and the Danish Data Protection Agency (2007-58-0015).

The study flow is presented in Figure 1 Study Flow PROLUCA. Using a 4-arm, randomized design, potential subjects will be identified and screened for eligibility and informed about PROLUCA by the study research coordinators at the involved hospitals (Bispebjerg University Hospital and Gentofte Hospital). After referral to intended curative lung cancer surgery at Copenhagen University Hospital (Rigshospitalet), the subjects are contacted by telephone and provided with a review of the study. If the subjects accept to participate, the baseline assessment is performed at Copenhagen Centre for Cancer and Health. At baseline the following assessments are performed: (1) PROs described in Table 2 Data Assessment Schedule in the PROLUCA Trial, (2) anthropometric data, (3) 6MWD, (4) muscle strength (1RM in chest- and leg-press machines), (5) pulmonary function test, and (6) cardiopulmonary exercise test (VO_2_peak). All baseline assessments will be completed as close to time of diagnosis as possible and repeated the day before surgery, pre-intervention (6MWD, pulmonary function, FACT-L), post-intervention, and at follow-up six months and one year after surgery.

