	**Physiological measurements**					
Cardiorespiratory capacity (VO_2_peak)	X	X		X	X	X
Six- minute walk distance (6MWD)	X	X	X	X	X	X
One-repetition-maximum (1RM)	X	X		X	X	X
Heart rate (HR), Blood pressure (BP)	X	X		X	X	X
Spirometric (FEV_1_/FEV_1_%)	X	X		X	X	X

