#### ***Analytic plan***

The intention-to-treat analysis includes all randomized participants in their randomly assigned allocations. The intervention group assignment will not be altered based on the participant's adherence to the randomly allocated study arm. Patients who are lost-to-follow-up are included in the analysis (intention to treat). For the primary analysis, a multiple regression model will be used to assess a change in VO_2_peak on study group, the baseline value of the endpoint, and other pertinent baseline variables that may influence change in the study endpoints (e.g., co-morbid conditions/medications, self-reported exercise history, age). Data from PROs will be presented as mean, standard deviation (SD), median and inter-quartile range (IQR) and all change scores (value at follow-up minus value at baseline) will be presented with a 95% confidence interval.

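### The continuous secondary endpoints are compared by unadjusted t-tests of change, which gives up precision that the collected baseline values would supply at no cost

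*Protocol article*

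**What the plan says.** Under Sample size calculation, the protocol article sets the comparison: "For each of the primary and secondary endpoints, three separate t-tests will be used to compare each experimental arm to the control arm". The quantity compared is the difference "in mean change across time of the endpoint". Holm's procedure is applied within each endpoint at an overall two-sided 0.05, so the smallest of the three p-values must fall below 0.0167.

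Under Analytic plan, a baseline-adjusted model appears, but for one outcome: "For the primary analysis, a multiple regression model will be used to assess a change in VO_2_peak on study group, the baseline value". For patient-reported outcomes that section adds only summary statistics, and says that "all change scores (value at follow-up minus value at baseline) will be presented with a 95% confidence interval". No adjusted model is given for any secondary endpoint.

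The baselines exist. The Procedure section says "At baseline the following assessments are performed: (1) PROs described in Table 2", and goes on to list 6MWD, 1RM, pulmonary function and the exercise test. Table 2 marks 6MWD, 1RM, spirometry, EORTC QLQ-C30, LC13, FACT-L, HADS and SF-36 at baseline. Group allocation (Randomization) places randomisation after the baseline assessments and stratifies it by VATS versus thoracotomy.

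**The concern.** A t-test of change subtracts the whole baseline value, which fixes the slope of follow-up on baseline at 1. For a test or questionnaire with visit-to-visit noise the slope is usually below 1, so subtracting the full baseline adds variance that a fitted slope would avoid. The sponsor already fits that slope for VO2peak. For the continuous secondary endpoints the article names a method, and it is the less efficient of two valid ones.

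At stake are wider confidence intervals and lower power than the same patients could give. This matters most for the patient-reported outcomes, which both specific aims name beside VO2peak, and because at least one comparison per endpoint must clear 0.0167 before any can be declared significant.

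**Working it through.** **Inputs from the protocol article.** 95 patients per arm; three arm-versus-control tests; first Holm level 0.05/3 = 0.0167, two-sided; for VO2peak, a relevant difference of 2 and a standard deviation of change of 4.0 mL/kg/min, so 2/4.0 = 0.5 standard deviations of change.

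**Assumptions.** The article gives no rho and no standard deviation for any secondary endpoint. rho is varied from 0.3 to 0.9. The effect of 0.5 standard deviations of change is borrowed from VO2peak for illustration, with 0.4 as a second case.

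**The plan's own figure.** The only planning figure is 95 per arm for 80% power on VO2peak. The normal approximation for a single comparison at alpha 0.0167 gives 2 × 4.0² × (2.394 + 0.842)² / 2² = 84 per arm for a difference of 2, and 76 for 2.1. The stated 95 is not reproduced without an attrition allowance that the article does not mention. That is a separate matter and does not bear on this point, which compares two analyses at the same 95 per arm.

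**Variance ratio.** Let both visits have standard deviation s.
- Change score: variance per patient = 2s²(1 − rho).
- Adjusted for baseline: residual variance per patient = s²(1 − rho²).
- Ratio = (1 − rho²) / [2(1 − rho)] = (1 + rho)/2.

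| rho | Variance ratio | Change in standard error | Adjusted n per arm matching 95 |
|---|---|---|---|
| 0.3 | 0.65 | −19% | 62 |
| 0.5 | 0.75 | −13% | 72 |
| 0.7 | 0.85 | −8% | 81 |
| 0.8 | 0.90 | −5% | 86 |
| 0.9 | 0.95 | −3% | 91 |

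Simulation at 95 per arm gave ratios of 0.66, 0.77 and 0.86 at rho 0.3, 0.5 and 0.7, against 0.65, 0.75 and 0.85 in theory.

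**Power.** Noncentral t, 95 per arm, two-sided alpha 0.0167; the adjusted effect is d / √[(1 + rho)/2].
- d = 0.5: 84.7% by t-test of change; adjusted, 94.0% at rho 0.5, 90.6% at 0.7, 88.7% at 0.8 and 86.7% at 0.9.
- d = 0.4: 63.4% by t-test of change; adjusted, 77.8% at rho 0.5 and 71.7% at 0.7.

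**Unequal standard deviations.** If the follow-up standard deviation is k times the baseline one, the ratio is k²(1 − rho²) / (1 + k² − 2k·rho). For k = 1.2 it is 0.87 at rho 0.5 and 0.97 at 0.7; for k = 0.8 it is 0.57 and 0.63. In large samples the ratio cannot exceed 1, so adjustment costs essentially nothing even where it gains little.

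**The case against.** The strongest objection is about reading. The t-test sentence sits under a sample size heading and covers primary and secondary endpoints together. For VO2peak the Analytic plan gives something else, so the sentence may be power-calculation language that was never meant to govern the analysis. The Analytic plan also justifies its covariates by their influence on study endpoints, in the plural. This has some force, and it is why the edit belongs with the VO2peak reconciliation. But the sentence says what will be done, it covers secondary endpoints for which no sample size is computed, and the regression sentence is confined to the primary analysis with VO2peak as outcome. Neither the heading nor the plural supplies an adjusted model for any secondary endpoint. Settling VO2peak alone would leave them with the t-test.

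Second, the t-test is sound. A reader might infer that secondary results would be biased by chance baseline imbalance or by regression to the mean. The documents do not support that. Chance imbalance averages to zero over randomisations and is already in the standard error, and regression to the mean acts equally on randomised arms in expectation. Type I error is not harmed. At rho 0.5, a baseline difference of one standard error (√(2/95) = 0.145 SD) does move the change estimate by about 0.145 × 0.5 = 0.07 SD, but only conditionally on that imbalance.

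Third, the size rests on an unknown rho. For d = 0.5 the power gain is 4.0 points at rho 0.8 and 2.0 at 0.9. Stable measures, perhaps FEV1, may gain little. This objection stands in full.

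**Conclusion.** The point holds as one of efficiency. For the continuous secondary endpoints, the only stated between-arm test leaves out baselines that the trial collects before randomisation and that the sponsor already uses for VO2peak. Because the article names the method, this is not detail left to a statistical analysis plan.

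The loss is in precision alone: with equal standard deviations, about 25% of variance at rho 0.5, 15% at 0.7, and 5% to 10% at 0.8 to 0.9. All values of rho are assumed, and the size will differ by instrument.

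It would be tempting to say that these comparisons carry half of the trial's question. The aims do name patient-reported outcomes, but VO2peak is the sole primary endpoint and power is defined on it alone; 6MWD, 1RM and FEV1 do not appear in the specific aims. Complications, survival and work status lie outside the point. The change is worth making because it is nearly free, not because the stated test is invalid.

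**What to change.** State in Sample size calculation and Analytic plan that each continuous secondary endpoint is analysed by regressing its follow-up value (or its change) on study group, that endpoint's own baseline value and the randomisation stratum, VATS versus thoracotomy. Apply Holm's procedure, at the same thresholds, to the p-values of the three arm-versus-control contrasts from that model. Keep raw change scores with 95% confidence intervals as descriptive summaries.

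Spell the model out rather than pointing to the VO2peak regression, whose further covariates are given only as examples. Make the edit together with the reconciliation of the t-tests and the regression for VO2peak, so that one statement says which model applies to which endpoint.

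The cost is a sentence or two of analysis text. No new data, visits or patients are needed.

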#### ***Analytic plan***

The intention-to-treat analysis includes all randomized participants in their randomly assigned allocations. The intervention group assignment will not be altered based on the participant's adherence to the randomly allocated study arm. Patients who are lost-to-follow-up are included in the analysis (intention to treat). For the primary analysis, a multiple regression model will be used to assess a change in VO_2_peak on study group, the baseline value of the endpoint, and other pertinent baseline variables that may influence change in the study endpoints (e.g., co-morbid conditions/medications, self-reported exercise history, age). Data from PROs will be presented as mean, standard deviation (SD), median and inter-quartile range (IQR) and all change scores (value at follow-up minus value at baseline) will be presented with a 95% confidence interval.

## Discussion

The aim of PROLUCA is to contribute with important knowledge about the efficacy of pre- and early postoperative rehabilitation in patients with NSCLC in a non-hospital setting.

The decision to target newly diagnosed patients with NSCLC was primarily based on the fact that these patients are not often examined in relation to the effect of rehabilitation, although they generally have a good performance status and prognosis after surgery and adjuvant chemotherapy. In consequence, the issue of NSCLC survivorship is becoming an increasingly important aspect of the multidisciplinary care of this patient group and the demands for knowledge correspondingly important.

The need for rehabilitation becomes obvious by the fact that NSCLC patients are subject to a marked decrease in cardiorespiratory capacity due to a combination of age and comorbidity and reinforced by the use of adjuvant cancer treatment [6]. It is well known that good preoperative cardiorespiratory capacity leads to better postoperative conditions resulting in less postoperative complications in patients with NSCLC [1,5]. Further studies are also warranted on other physical effects of exercise and how to commit this group of cancer patients to a more active lifestyle.

Studies focusing on the effects of exercise interventions pre- and postoperatively are required to fully understand the potential effect of exercise over time. The optimal characteristics of exercise (mode, intensity, frequency, duration, and timing) have yet to be determined [24].

No published research in cancer rehabilitation has investigated the best timing of rehabilitation in patients with NSCLC in a randomized clinical trial. Qualitative studies have pointed out that cancer patients may experience transition points during time of illness to which they are particularly vulnerable: (1) diagnosis, (2) operation and hospitalization, (3) transition from hospital to daily life, and (4) return to daily life [66-72]. The timing of rehabilitation has also been indicated to of importance when it comes to motivation toward a healthier life style in patients with a variety of cancer diagnoses [73]. The ‘teachable moment’ is a term used in e.g. research in breast cancer patients describing the transition that takes place when the patients are diagnosed. This transition can modify barriers and motivate the patient; thus timing of rehabilitation is of great importance for the outcome [74].

The PROLUCA study aims at revealing the impact of timing of rehabilitation on VO_2_peak and health-promoting behavior in patients with NSCLC. The effect six months and one year after surgery is measured. VO_2_peak is chosen as the primary endpoint as this test provides the gold standard (direct) assessment of cardiorespiratory capacity [13]. In a hospital setting it would have been interesting to test cardiorespiratory capacity as early as two weeks postoperatively, but as the intervention in PROLUCA is carried out in a non-hospital setting, this is not possible due to safety reasons. According to the Danish Health Act from 2007 the responsibility for rehabilitation of all patients with a decrease in functional capacity lies with the municipalities unless medical assistance is needed. The same is true of patient-targeted prevention.

The patients perform a VO_2_peak test preoperatively and again after the intervention. The first test acts as a surrogate parameter for the starting point, and PROLUCA is therefore not capable of clarifying what happens to VO_2_peak shortly after surgery. Research indicates that VO_2_peak spontaneously recovers to a limited degree at approximately 3 months after surgery and stabilizes at approximately 6 months after pulmonary resection. Another study finds a 13% decrease in VO_2_peak ~6 months after surgery [75]. As this study compares the preoperative VO_2_peak with postoperative VO_2_peak value 6 months after surgery, the best estimate possible is chosen.

To obtain a patient population as close to normal daily practice as possible where patients are suffering from a variety of comorbidity, PROLUCA limits the amount of exclusion criteria. This makes PROLUCA unique compared to other studies whose selection of patients is distinct. Therefore the results of PROLUCA may contribute importantly to daily clinical practice.

With the increasing interest in the field of exercise-oncology research, more studies are now focusing on the application of exercise as a concomitant intervention alongside anti-cancer therapies.

